## Abstract

**Background:**

Access to methadone treatment can reduce opioid overdose death by up to 60%, but US patient outcomes are suboptimal. Federally allowed methadone treatment accommodations during the COVID-19 public health emergency were not widely adopted. It is likely that staff-level characteristics such as trauma symptoms influence the adoption of treatment innovation.

**Objective:**

Methadone Patient Access to Collaborative Treatment (MPACT) is a 2-phased project (pilot and field trial) to develop and test a staff-level, multimodal intervention to increase staff adoption of low-barrier, patient-centered methadone treatment practices and ultimately improve treatment retention and patient outcomes.

**Methods:**

A pilot and national trial will measure implementation feasibility, acceptability, and effects of the MPACT intervention on treatment practice change, clinic culture, patient retention, and patient posttraumatic stress symptoms (PTSS). The pilot will be a single-arm 5.5-month pilot study of MPACT conducted in 2 Arizona methadone treatment clinics (rural and urban) among 100 patients and 22 staff. The national trial will be a 20-month cluster randomized trial conducted among 30 clinics, 600 patients (20 per clinic), and 480 staff (18 per clinic). Data will be gathered by staff and patient surveys and patient chart review. The primary study outcome is increased patient methadone treatment retention measured as (1) time to first treatment interruption from study enrollment; (2) active in treatment at enrollment, day 30, 60, 90, and 120; and (3) continuous days in treatment during the study period. Secondary study outcomes include reductions in vicarious trauma and PTSS among enrolled opioid treatment program staff and PTSS among enrolled patients.

**Results:**

The pilot study was funded by the National Institute on Drug Abuse (award R61DA059889, funded September 2023), and the field trial will be funded under the associated R33 mechanism in September 2025. The pilot study was completed in March 2025. The randomized controlled trial will begin in December 2025. Both the pilot and trial have been approved by the University of Arizona Human Subjects Protection Program and have been registered with the clinical trials network.

**Conclusions:**

The MPACT study will provide a foundation for an evidence-based, staff-level intervention aimed at improving patient retention in methadone treatment. Future studies should examine the individual components of MPACT to determine their differential contributions to the primary outcome of patient methadone treatment retention and to secondary outcomes of staff and patient reduction in stress symptoms.

**Trial Registration:**

ClinicalTrials.gov NCT06513728; https://clinicaltrials.gov/study/NCT06513728 and ClinicalTrials.gov NCT06556602; https://clinicaltrials.gov/study/NCT06556602

**International Registered Report Identifier (IRRID):**

DERR1-10.2196/69829

## Introduction

### Background

Methadone is one of the most essential tools available to reduce opioid overdose deaths because it is safe, effective, and patient-preferred for the treatment of opioid use disorder (OUD) [1-3]. Access to methadone, one of 2 safe and effective OUD treatments, can reduce overdose mortality by up to 60% [4,5]. However, the promise of methadone is significantly diminished by geographic maldistribution of clinics and variations in the delivery of methadone maintenance treatment (MMT) across the country [6-8]. Treatment variations likely produce the observed wide-ranging MMT retention rates (30%-84%) [9,10].

MMT in the United States is delivered only by opioid treatment programs (OTPs; “methadone clinics”) certified and accredited by the federal government [11]. Variation in treatment quality and access maldistribution means that the impact of poor MMT outcomes is felt most acutely in rural communities as well as among populations who are Black, Hispanic, or Indigenous [12]. Unlike other health care environments, OTPs serve a daily average of more than 100 people in a narrow time window [13] and have been described as feeling “like bus stations” [14] rather than medical clinics. OTPs have been criticized as being unresponsive to patient need for treatment flexibility [15] and are not equipped to address what we know to be higher rates of patient trauma exposure and posttraumatic stress symptoms (PTSS) compared to the general population [16,17]. While MMT outcomes can be impeded by patient trauma [18], it is also possible that poor MMT outcomes and patient trauma are exacerbated by OTP practice and culture [19,20]. Patients report disenfranchisement from treatment decision-making through language referring to dosing as “privileges,” staff behavior described as “carceral” [21], and being tied to the OTP by “liquid handcuffs” due to daily required in-clinic supervised dosing [22].

Policy and systems evolution is occurring to improve the way MMT is delivered in the United States. Unprecedented US regulatory change during the COVID-19 public health emergency [23] and again in February 2024 [11] permitted and then further clarified methadone dosing and delivery flexibility so that treatment was more individualized and patient-centered. However, as has been observed, policy changes during the COVID-19 public health emergency were insufficient to ensure sustained changes [24-26]. This is likely the result of multiple factors hindering the implementation of MMT innovation. Implementation science suggests that in addition to the outer setting factor of federal policy, there are inner setting factors that likely influence the adoption of MMT treatment innovation [27]. These include clinic organizational characteristics and culture as well as staff characteristics and staff beliefs. Figure 1 displays our current thinking about hypothesized relationships between and among inner setting factors, adoption of innovation, and patient outcomes.

Staff trauma is one particular inner setting factor that is linked to the adoption of innovation and quality of treatment delivery. A preliminary study by several authors here suggests that OTP staff trauma may play a central role in shaping clinic culture and methadone treatment practice changes [14]. Evidence from studies among other types of health professionals demonstrates that vicarious trauma (VT), or work-related trauma (ie, coexperiencing patient distress and change in worldviews because of ongoing distress), is associated with reduced staff empathy and increased PTSS [28]. VT outcomes include burnout, reduced patient empathy and compassion satisfaction, low morale, impaired clinical decision-making, and compromised patient care [29-31]. The only extant study of OTP staff trauma histories and symptoms found that 63% of staff exhibited PTSS at clinical levels, indicating a need for treatment [32]. Therefore, a potential strategy to facilitate the adoption of MMT innovation is to implement staff-level interventions aimed at reducing PTSS and VT while providing training about low-barrier, patient-centered methadone treatment.

**Figure 1 figure1:**
[figure not shown]
Potential inner setting factors impacting methadone treatment outcomes.

To this end, we developed Methadone Patient Access to Collaborative Treatment (MPACT): a multimodal intervention to increase staff awareness of and readiness to adopt MMT treatment innovation. MPACT promotes treatment flexibilities allowed by federal regulators and patient-centered, trauma-informed MMT and seeks to empower OTP staff and clinic groups to adopt these treatment flexibilities by addressing staff VT and PTSS, which will improve treatment quality and ultimately MMT retention. The objective of this study is to test the adoption, feasibility, and impact of MPACT on methadone treatment delivery and patient outcomes. There are 6 specific aims for the MPACT study over the 6-year project period. The specific aims are listed here and will be described in the following subsections.

### Phase 1, Years 1-2: MPACT Intervention Development and Pilot Testing

Phase 1 aims (1) to develop MPACT through multilevel, iterative planning with methadone clinic staff and people with recent methadone treatment experience; (2) to determine MPACT implementation feasibility, acceptability, and preliminary effect on methadone treatment practice change and clinic culture; and (3) to determine the preliminary effect of MPACT on methadone treatment retention and patient PTSS.

### Phase 2, Years 3-6: Hybrid, Cluster Randomized Controlled Trial

Phase 2 aims (4) to quantify the effects of MPACT on methadone treatment practice change and clinic culture, (5) to determine the efficacy of MPACT on methadone treatment retention and patient and staff PTSS outcomes, and (6) to evaluate the effect of patient and staff trauma on primary outcomes and staff MPACT implementation.

## Methods

### Ethical Considerations

The MPACT study protocol and related documents were reviewed and approved by the University of Arizona Human Subjects Protection Program (pilot: #STUDY00003631 and trial: #STUDY00005677), the single institutional review board overseeing all sites participating in the study: University of Arizona, Indiana University, Western Michigan University, and Columbia University. All participants will engage in a web-based informed consent process prior to study enrollment. The consent will be downloaded and retained by the study as documentation. Patient participants will consent to both survey participation and the release of specified elements of their clinic medical record for the purpose of the study. Confidentiality of staff and patient participants in the enrolled MPACT clinics will be preserved by making every effort to prevent the clinic leadership and staff from knowing which patients are enrolled as study participants and keeping clinic leadership and patients from knowing which staff are enrolled as study participants. Unique identifiers will be created at the time of enrollment and used throughout the study period. All study personnel (staff and investigators) have been trained in human participant protection through the completion of Social Behavioral Research and Biomedical Research modules with the Collaborative Institutional Training Initiative program and the completion of conflict of interest training and have annually declared conflicts of interest for review by the University of Arizona Human Subjects Protection Program. All reported data will be aggregated and deidentified. All information will be stored in a secure and encrypted drive and accessible only by the principal investigator ([name]) and the study coordinator (SY). The study was registered under ClinicalTrials.gov (NCT06513728 for the phase 1 pilot and NCT06556602 for the phase 2 trial). Participants will be offered financial remuneration totaling US $100 for the completion of all 5 surveys on time and during the pilot study period and US $160 for the completion of surveys on time and during the trial study period.

### Phase 1, Years 1-2: MPACT Intervention Development and Pilot Testing

#### Overview

Aim 1: Develop MPACT through multilevel, iterative planning with methadone clinic staff and people with recent methadone treatment experience.

MPACT is an experimental intervention comprised of 4 evidence-based components adapted by a group of people who have been in methadone treatment within the past 5 years in Arizona, a group of OTP staff in all clinic roles (front desk, peer support staff, case management, counseling, clinical supervision, medical, and administrative) from 3 Arizona OTPs (2 urban and 1 rural), and a group of subject matter experts focused on clinical supervision, human resources, and employee education.

The adaptation of MPACT components was accomplished through an iterative codevelopment process involving OTP staff and methadone community (patient) groups. The creation of a trauma-informed codevelopment space was crucial to facilitate safer and more open discussions. To accomplish this, we established a parallel, intervention refinement process using a helical structure developed by this team and based on our prior research with structural indicators for community-based participatory action research [33]. As shown in Figure 2, the “hand off” of work drives an iterative (helical) thinking process. This structure provides distinct spaces for thoughtful dialogue within and between each group.

The outcome of the codevelopment process was a robust multimodal intervention (MPACT) comprised of the following 4 elements.

**Figure 2 figure2:**
[figure not shown]
Trauma-informed, collaborative development structure to refine MPACT components. MPACT: Methadone Patient Access to Collaborative Treatment; OTP: opioid treatment program.

#### Accredited Psychoeducational Training

A jointly accredited, self-paced, 3-module psychoeducational training focused on (1) the definition and application of low-barrier, patient-centered, trauma-informed methadone treatment; (2) public and clinic policy (federal and state); and (3) clinic staff opportunities to increase patient-centered, trauma-informed methadone treatment. The training seeks to empower staff to initiate any positive change at the individual and staff group levels. Joint accreditation offers continuing medical education for physicians and nurses as well as continuing education credits for social workers, psychologists, peer support specialists, case managers, and administrators. Training completion is incentivized by the award of 3 free continuing education credits according to professional discipline. While training is voluntary, to receive the continuing education credits, staff of MPACT-enrolled clinics must complete the training within 2 weeks of the MPACT launch within the clinic. New staff can complete the training as they are hired during the MPACT intervention period. This modular training approach was adapted from a prior successful project focused on increasing pharmacy syringe sales to people who use drugs [34].

#### Staff Wellness Education and Assessment

All staff in MPACT-enrolled clinics will receive training about trauma exposure and reactions, trauma-informed methadone treatment, availability and modalities of trauma treatment, and VT through curated presentation materials. These materials will be accessible to all staff through an MPACT web portal and through training or communications as determined by the enrolled clinics. The training materials include video and visual content designed for easy integration into clinic employee training, onboarding, or as refresher training. As part of the training, staff will be introduced to an anonymous web-based “wellness” screener, which includes an 8-item posttraumatic stress disorder symptoms screener (Posttraumatic Stress Disorder Checklist [PCL-5]) [35,36] and an 8-item Vicarious Trauma Scale [37]. Individual screening outcomes (results) trigger a curated and immediately presented message regarding self-care, referral to the VA PTSD Coach [38,39] (a downloadable, free application) and referral to the employee assistance program offered as a behavioral health benefit to employees where indicated. Employees will have access to wellness training throughout the MPACT intervention period and can use the self-screener repeatedly if desired. The screener will also be “advertised” in staff-only areas with a curated poster on stress, including a link or QR for easy access.

#### Trauma-Informed Clinic Self-Assessment

A trauma-informed clinic self-assessment (TICA) will be conducted quarterly during the study period. TICA assessment outcomes are generated by data from aggregated responses to a 16-item anonymous survey of staff measuring staff development, available resources, support, safe physical environments, trauma-informed policies, and patient-centered practices specific to methadone clinics. Items were selected and modified by the study team using an organizational trauma-informed practice tool as a reference instrument [40]. Summarized results are discussed with clinic leadership who will decide how and when to share them with clinic staff.

#### Reflective Supervision Consultation

Reflective supervision is an evidence-based professional development intervention focusing on the relationship and process of collaborative case consultation and reflection for clinicians providing psychosocial support [41,42]. Reflective supervision provides strategic guidance to increase self-reflectiveness and self-awareness and encourages participants to independently process clinical encounters and solve challenges. These skills have been shown to improve patient care [43,44]. To our knowledge, there are no existing reflective supervision consultation models tailored to OTP staff. Therefore, we adapted the standard reflective supervision practices to apply and be accessible to all OTP staff who have intensive and consultative interactions with patients. These staff roles include case managers, counselors, and peer support. Reflective supervision will begin in month 1 of the intervention period and will continue on a biweekly basis throughout the intervention period for each MPACT-enrolled clinic. Sessions are facilitated by a trained reflective supervisor who will also be trained by the MPACT study clinician.

Aim 2: Determine MPACT implementation feasibility, acceptability, and preliminary effect on methadone treatment practice change and clinic culture.Aim 3: Determine the preliminary effect of MPACT on methadone treatment retention and patient PTSS.

A single-arm 5.5-month pilot study of MPACT will address aims 2 and 3 and involves 2 Arizona-based OTPs (1 rural and 1 urban), 100 patients, and 22 staff (25 patients and 6 staff of the rural clinic and 75 patients and 16 staff of the urban clinic). Data collection will be accomplished through a web-based survey of staff and patient participants monthly during the pilot study period, which began in October 2024 and ended in March 2025. The 4 elements of MPACT intervention were delivered during the 4-month period following study recruitment. Eligibility criteria for study inclusion included being 18 years of age or older, being a staff member or a patient at 1 of the 2 pilot clinics, being willing to participate in monthly surveys during the pilot study period, and (for patients) agreeing to share selected components of their medical charts with the study team.

### Measures

The primary study outcome is increased patient methadone treatment retention. This outcome is measured in three ways: (1) time to first treatment interruption, calculated as the number of days to first missed dose from day 0 (MPACT enrollment); (2) evidence of being active in treatment, a binary (yes or no) if receiving dose at points in time on day 0, 30, 60, 90, and 120; and (3) continuous days in treatment during the study period, calculated as time (days) to discharge. Data measuring this outcome are gathered by patient surveys and chart reviews.

Secondary study outcomes include reductions in VT and PTSS among enrolled clinic staff and PTSS among enrolled patients. Data measuring secondary outcomes are gathered by a survey of staff and patients enrolled in the study. For staff and patients, PTSS are measured using the 8-item posttraumatic stress disorder symptoms screener otherwise known as the PCL-5 [35]. Staff VT is measured by the Vicarious Trauma Scale [37], burnout is measured by a 3-item scale [45], and compassion satisfaction and compassion fatigue are measured by the shortened, 9-item Professional Quality of Life Scale for staff [46].

The degree to which methadone treatment is patient-centered is also a secondary outcome measured through staff surveys (assessing whether they believe they are providing it) and patient surveys (assessing whether they feel they are experiencing it). Patient-centered care competency is measured by a 19-item scale [47] including the following subscales: respecting patient perspectives, promoting patient involvement in the care process, providing patient support, and advocating for patients. Patient-centered care, as defined by the study team, is measured using a 5-item instrument that reflects the concepts of patient-centered care introduced during the accredited training modules. This scale is administered to staff, with an adapted version used for patients.

Other individual-level variables of interest for the staff participants include (1) personal characteristics—demographics, personal substance use disorder and treatment experience, and trauma exposure history (measured by the Life Events Checklist-5) [48]; (2) work characteristics—training, education, and licensure related to their clinic role; (3) empowerment using a 5-item empowerment scale [49]; (4) stigma—toward people with OUD with a 9-item scale [50], self-stigma with a 9-item scale [51], and fear of enacted stigma through a 9-item scale [52]; (5) beliefs—about trauma-informed care measured by the attitudes toward trauma-informed care [53] and about abstinence measured by the Abstinence Orientation Scale [54]; (6) comfort with targeted practices related to the most recent federal changes to methadone treatment delivery measured by items adapted from prior studies measuring comfort with practices [34,55,56]; and (7) fidelity to MPACT—the degree to which the clinic implements the MPACT intervention.

Other individual-level variables of interest for the patient participants include (1) personal characteristics—demographics, housing, trauma history (Life Events Checklist-5), and trauma symptoms (PCL-5); (2) methadone treatment—time in treatment and dose sufficiency; (3) empowerment—as measured by a 15-item scale [57] and through an adapted 16-item Kim Alliance Scale [58]; and (4) fidelity to MPACT—the degree to which the clinic implements the MPACT intervention.

As this is a hybrid (implementation and effectiveness) pilot and trial, we are specifically focused on reach, implementation, adoption, and (in the trial) maintenance using the RE-AIM (Reach, Effectiveness, Adoption, Implementation, and Maintenance) framework [59]. Measures collected for the pilot will also be collected for the trial.

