### Data Collection

Primary and secondary study outcomes will be measured by surveys and patient chart reviews. Surveys will be administered monthly for the pilot study: assessment 1 (baseline at enrollment) and assessment 2-5 in 30-day sequences through the study period, with a contact reminder at day 27 and a completion forgiveness period of 5 days (day 35). Table 1 displays the sequencing of measures across the 5 pilot surveys.

**Table 1 table1:** Sequencing of Methadone Patient Access to Collaborative Treatment (MPACT) primary and secondary measures (assessment 1-5).

Construct		Assessment 1 (enrollment)			Assessment 2		Assessment 3		Assessment 4		Assessment 5 (study conclusion)
		Staff items, n	Patient items, n								

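### In the single-arm pilot the retention clock starts at patient enrolment, but MPACT was delivered only after recruitment, so some outcomes scored under MPACT precede it

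*Protocol article*

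**What the plan says.** Under Measures, the first retention outcome is time to first interruption, "calculated as the number of days to first missed dose from day 0 (MPACT enrollment"). The second is "a binary (yes or no) if receiving dose at points in time on day 0, 30, 60, 90, and 120". The Abstract words the origin as "time to first treatment interruption from study enrollment", and Data Collection describes the pilot surveys as "assessment 1 (baseline at enrollment) and assessment 2-5 in 30-day sequences through the study period". Taken together, day 0 is the patient's own enrolment.

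The pilot timetable stands at the end of the Reflective Supervision Consultation section: "A single-arm 5.5-month pilot study of MPACT will address aims 2 and 3", and "The 4 elements of MPACT intervention were delivered during the 4-month period following study recruitment". The same section says "Reflective supervision will begin in month 1 of the intervention period". Nothing in the article moves day 0 to the start of MPACT in the clinic, although the section on accredited training refers to a clinic launch when it sets the training deadline.

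The Phase 2 Overview uses the pilot to set the preliminary effect size and confirm the trial's power. Statistical Analysis treats 66% interruption at 12 months as provisional until the pilot confirms it, and names time to first interruption as the trial's primary outcome.

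**The concern.** The clock and the intervention start at different times. MPACT works on staff and clinics, so a patient cannot be exposed before the clinic launches it. A patient who enrols early in recruitment and misses a dose before launch has already had the primary event, and nothing after launch can change that patient's result. Some day-30 checks likewise describe usual practice.

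The pilot has no comparator to absorb these events. Its estimate on the enrolment clock is a mixture: neither an interruption rate under MPACT nor a rate under usual care. That mixture would then feed the trial's effect size and event rate.

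**Working it through.** **Inputs from the article.** Pilot length 5.5 months; delivery 4 months, after recruitment; checks at days 0, 30, 60, 90 and 120; interruption 66% at 12 months.

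**Assumptions, not in the article.** The whole difference between 5.5 and 4 months lies before launch; enrolment is uniform over it; the hazard is constant; MPACT has no effect in the 120 days.

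**1. Pre-launch window.** 5.5 − 4 = 1.5 months, about 45 days.

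**2. A patient enrolled on the first day.** The day-30 check falls 45 − 30 = 15 days before launch. Exposed time is 120 − 45 = 75 of 120 days.

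**3. Day-30 checks before launch.** These belong to patients who wait more than 30 days: (45 − 30)/45 = one third.

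**4. Exposed share of the 120 days.** The mean wait is 22.5 days, so (120 − 22.5)/120 = 81%.

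**5. Hazard.** −ln(1 − 0.66) = 1.079 per 365 days.

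**6. First interruptions by day 120.** 1 − exp(−1.079 × 120/365) = 29.9%.

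**7. First interruptions before launch.** Put a = 1.079 × 45/365 = 0.133. The mean of 1 − exp(−1.079u/365) over u from 0 to 45 is 1 − (1 − exp(−a))/a = 6.4%. Share of 120-day events: 6.4/29.9 = about 21%.

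**8. Range.**
- If every patient waited the full 45 days: 1 − exp(−0.133) = 12.5% before launch, and 12.5/29.9 = about 42% of events.
- If every patient enrolled just before launch: 0%.
- The hazard matters less than the enrolment pattern. With uniform enrolment and a very low constant hazard, the share tends to 22.5/120 = 18.75%, and it rises with the hazard.
- If MPACT reduced interruptions after launch, the denominator would shrink and the share would rise.

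**9. The trial, as a conditional illustration only.** The article's own power figure is reproduced first. With constant hazards, HR = ln(0.45)/ln(0.34) = 0.740. Events are 300 × (0.66 + 0.55) = 363. Schoenfeld's formula, two-sided 0.05, gives power of 81.8%, which agrees with the stated figure of more than 80% without clustering. Now suppose patients enrolled before launch by a common lag, with HR 1 until launch and 0.740 afterwards, and weight the log HR by the share of events after launch:

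| Assumed lag (months) | Average HR | Power at 12 months, no clustering |
|---|---|---|
| 0 | 0.740 | 81.8% |
| 0.5 | 0.756 | 75.9% |
| 1 | 0.772 | 69.6% |
| 1.5 | 0.787 | 63.0% |

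With 20 months of follow-up, a 1.5-month lag gives 78.6%, against 90.4% with none. The article states no lag for the trial.

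**The case against.** The strongest objection is that only the pilot has a documented lag. The sentence placing delivery after recruitment describes the pilot. For the trial, the article gives recruitment steps and staggered site starts, but not whether patients enrol before their clinic launches. Carrying the measures over does not carry over the delivery schedule. This stands. A reader might infer that the trial estimate is diluted and its power cut to a definite figure; the documents do not support that.

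A reader might also infer that day 0 is undefined for control patients because they are never enrolled in MPACT. That does not hold: MPACT is also the name of the study, and the Abstract's enrolment date exists in both arms. Nor do the day 30 to 120 checks carry into the trial analysis as they are. Statistical Analysis uses 1, 3, 6 and 12 months there, as secondary outcomes.

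On the pilot, it can be said that it is complete, mainly about implementation, and offers only a preliminary indication of effect, and that the 45 days come from a subtraction. All true. Part of the 1.5 months might be close-out, or the two clinics might have launched at different times. But the stated order, delivery after recruitment, remains, and the article gives the pilot estimate a job in planning the trial. Reading "MPACT enrollment" as clinic enrolment does not help, because in the recruitment steps given for the trial the clinic is enrolled before patient flyers go up.

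Finally, starting the clock at launch has its own cost. In the trial, a primary risk set of patients still in treatment at launch could drop patients after randomisation on the outcome itself, and differently by arm. It would not guarantee proportional hazards either, since an effect working through staff would probably build gradually. This stands and shapes the fix.

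**Conclusion.** The point holds for the pilot. The article fixes day 0 at patient enrolment and places delivery after recruitment, so up to about 1.5 months of counted time precedes MPACT for the earliest patients. On the stated assumptions, about 21% of 120-day first interruptions and one third of day-30 checks precede launch; the actual enrolment and launch dates could put the first figure anywhere from 0% to about 42%. The importance lies in the use of the pilot to confirm the trial's effect size and 66% rate.

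For the randomised trial the point is conditional. If patients do enrol before launch, the enrolment clock still gives a valid randomised comparison, but one diluted towards no effect. The table above shows how sensitive power would be to such a lag; it does not estimate the trial's power.

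**What to change.** **Pilot.** Compute the retention measures from the clinic's MPACT launch date, or from enrolment if later. Patients still in treatment at launch enter then, whatever they missed before. Report pre-launch missed doses separately as baseline, and keep the enrolment clock as a sensitivity analysis. Use the launch-clock figures to confirm the trial's assumptions. The pre-launch missed doses are the pilot's only unexposed data on the usual-care rate.

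**Trial.** State when launch falls relative to patient enrolment, and record one launch date per clinic in both arms (start of MPACT or of the control training). If patients enrol before launch, keep every enrolled patient in the primary enrolment-based analysis. Add a pre-specified supplementary analysis, either with delayed entry at launch or with exposure as a time-varying covariate.

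**Cost.** A few sentences of wording, one date per clinic and some extra analysis. The chart review already asks for treatment dates, dosing and case notes that record missed doses. In the pilot, patients who leave treatment before launch drop out of the launch-clock estimate and must be reported separately.
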